**Methods:**

The study is a randomised controlled wait-list trial (RCT; *N* = 240). The intervention group will receive protocol-based MCT and work-focused interventions immediately after inclusion. The control condition is a wait-list control group. All patients will receive up to 12 weekly sessions. The study context is a Norwegian outpatient clinic part of a national programme aimed at reducing sick leave. The co-primary outcomes are change in RTW and symptoms of depression and anxiety at the end of treatment. In addition to self-report, sick leave will also be collected from national registries from 2 years prior to intervention to 4 years after intervention. Symptoms of depression and anxiety will be collected by self-report at pre- and post-treatment and at 6 and 12 months follow-up after treatment. A cost-effectiveness analysis will use total cost and quality-adjusted life-years as the secondary outcomes.

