### Sample size estimate

Sick leave will be operationalised as a percentage of sick leave collected both from the national registry and self-report. To evaluate the intervention versus wait-list condition, the percentage of sick leave status of the intervention group will be compared at end of treatment to the status of the control group at the end of the waiting period. The minimum expected effect is that of the treatment reported in the naturalistic follow-up study at the same clinic [56]. Data from this study showed a self-reported full RTW response rate of 0.41 in the intervention group versus 0.26 in the wait-list control group, with a pooled standard deviation of 0.4 [34]. Given this result, to detect differences in a dichotomous outcome variable we would need approximately 120 in each treatment group to have an 80% chance of detecting a significant difference at a two-sided significance level of 0.05 [63]. For the anxiety and depressive symptoms, detecting a 5 point difference between intervention and waitlist control group using a pooled standard deviation of 6.95, we need approximately 31 participants in each of the group in order to have an 80% chance of detecting a significant difference at a two-sided significance level of 0.05 [28, 64].

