### Data analysis and data management

Data analysis will be conducted in accordance with a pre-specified data-analysis plan. All data will be analysed based on an intention-to-treat (ITT) approach, and analyses will include all randomised patients. The primary outcomes are continuous measures in a repeated design, therefore linear mixed-model analysis (LMM) will be run. For effects on depression and anxiety, reliable clinical change index and Cohen’s *d* for effect size will be reported, the difference between groups will be analysed using mixed model ANOVA.

All data is recorded and managed in accordance with national health service guidelines. Access to data is managed by Diakonhjemmet Hospital.

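### The sick-leave co-primary is sized as yes/no full return to work but planned as a continuous percentage from two unranked sources, and the binary figure itself gives about 69% power, not 80%

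*Protocol article*

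**What the plan says.** All places are in the protocol article.

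- **Abstract, Methods:** "The co-primary outcomes are change in RTW and symptoms of depression and anxiety at the end of treatment".
- **Primary objectives and Sick leave (under Primary outcome measures):** degree or percentage of sick leave, from registry data and from self-report, listed side by side with no order of priority.
- **Sample size estimate, definition:** "Sick leave will be operationalised as a percentage of sick leave collected both from the national registry and self-report". The same section says that this percentage is compared between the intervention group at end of treatment and the control group at end of waiting.
- **Sample size estimate, calculation:** a "self-reported full RTW response rate of 0.41 in the intervention group versus 0.26 in the wait-list control group". The pooled SD is put at 0.4, leading to "to detect differences in a dichotomous outcome variable we would need approximately 120 in each treatment group" for an "80% chance of detecting a significant difference at a two-sided significance level of 0.05". Symptoms have their own calculation: 5 points, SD 6.95, about 31 per group.
- **Data analysis and data management:** "The primary outcomes are continuous measures in a repeated design, therefore linear mixed-model analysis (LMM) will be run". A further sentence, which opens with depression and anxiety, adds that "the difference between groups will be analysed using mixed model ANOVA".

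**The concern.** A power statement tells the reader how likely the planned test is to succeed under a stated effect. Here the effect is a difference in the proportion fully back at work, by self-report, while the planned test compares mean percentage of sick leave, perhaps from the registry. A patient who moves from full to half-time sick leave counts in the second and not in the first. The article gives no mean difference and no SD for the percentage, so the one cannot be translated into the other.

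Two things are at stake. The number that sets N = 240 has no link to the sick-leave test that will be reported, so a null result could not be judged against a known chance of detection. And with two unranked sources, the one that carries the conclusion could be settled after the results are seen.

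**Working it through.** **Inputs** (Sample size estimate; allocation from Randomisation and blinding): p1 = 0.41, p2 = 0.26, difference 0.15; stated SD 0.4; two-sided alpha 0.05, z = 1.960; power 80%, z = 0.842; 120 per arm. Symptoms: difference 5, SD 6.95.

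**1. The plan's 120 per group as a comparison of two proportions.**

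n = [z_a √(2p̄(1−p̄)) + z_b √(p1(1−p1) + p2(1−p2))]² / (p1−p2)², with p̄ = 0.335.

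- First term: 1.960 × √0.4456 = 1.308.
- Second term: 0.842 × √0.4343 = 0.555.
- n = (1.863)² / 0.0225 = 154.2, so 155 per arm.

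The stated figure is not reproduced. Variants give 152 (unpooled variance), 154 (arcsine) and 168 (continuity correction). The rates to three decimals given in the Background (0.414 and 0.263) give 153.

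**2. Power at 120 per arm.** (0.15 × √120 − 1.308) / 0.659 = 0.508, and Φ(0.508) = 0.69. The unpooled form gives 0.70.

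**3. Possible origins of 120.**

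- Means formula with the stated SD: 2 × (1.960 + 0.842)² × 0.4² / 0.15² = 111.6, so 112 per arm; power at 120 is 83%. This is not 120, and the SD does not fit the rates: √[(0.2419 + 0.1924)/2] = 0.466.
- One-sided 0.05 with proportions: 122 per arm. This is close to 120 but contradicts the stated two-sided level.

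The document does not show which route, if either, was taken.

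**4. The symptom calculation.** 2 × (2.802)² × 6.95² / 5² = 30.3, so 31 per arm. This reproduces. It is on a continuous scale, as is the planned symptom comparison, and power at 120 per arm exceeds 99.9%.

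**5. What 120 per arm can detect on the percentage scale.** Standardised difference = 2.802 × √(2/120) = 0.36 at 80% power and two-sided 0.05. The SD of percentage of sick leave is not in the document, so the values below are assumptions:

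| Assumed SD (percentage points) | Detectable difference, 80% power | Power for a 10-point difference |
|---|---|---|
| 30 | 10.9 | 73% |
| 35 | 12.7 | 60% |
| 40 | 14.5 | 49% |
| 45 | 16.3 | 41% |

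These are simple two-sample figures. Baseline adjustment and repeated measures would improve them by an amount that the document does not allow one to compute.

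**The case against.** The strongest reply is that the form of the outcome is nearly settled. The hypotheses, the primary objectives, the outcome description and the sample size section all speak of percentage or degree of sick leave, and the analysis section calls the primaries continuous. On that view only the abstract and the power calculation are out of line, and a separate analysis plan, mentioned but not shown, may say the rest. Most of this is fair. It leaves the source open, however, and it confirms that the calculation was done for a different variable. That conflict lies in the article's own text and is not a detail left to another document.

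Four stronger readings are tempting, and the document does not support them.

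- *Sick leave is to be analysed by two different models.* Only the linear mixed model covers sick leave. The ANOVA wording is tied to depression and anxiety.
- *No primary outcome has a valid power statement.* The symptom calculation reproduces and fits its planned comparison.
- *The ANOVA would drop patients with a missing visit.* That holds for one common form of repeated-measures ANOVA, but the term is also used loosely for F-tests from a mixed model. The same section asks for all randomised patients, and deletion of cases is not stated.
- *Several primaries at 5% inflate the family-wise error.* That requires a rule that any one success suffices, and no such rule is stated. The main hypothesis joins symptoms and sick leave; if all must succeed, there is no inflation. The 0.05 is a sample-size input, and multiplicity is commonly left to the analysis plan.

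**Conclusion.** The point holds for sick leave. The 80% power at 120 per group refers to binary self-reported full RTW and to no sick-leave test that the article describes. Taken on its own terms it is also overstated: about 69% with the stated rates and two-sided level, against a need of about 155 per arm. Both results use only figures from the article and standard formulas.

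The power of the planned percentage comparison is unknown. The detectable standardised difference of 0.36 is firm for an unadjusted two-group comparison with 120 analysed per arm; its translation to 11 to 16 percentage points rests on the assumed SD range. The symptom outcomes are adequately sized on the plan's own inputs. For them the only fault is that two model names are given where one should stand.

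**What to change.** 1. **Primary objectives, Sick leave and Abstract.** Before any unblinded analysis, name one source and one form for the sick-leave primary. Registry percentage of sick leave is a reasonable example, since Retention and follow-up describes registry data as less exposed to loss. Self-report then becomes supportive and full RTW a named secondary.
2. **Sample size estimate.** Attach the 0.41 versus 0.26 calculation to full RTW, restate its power as about 69% at 120 per arm, and remove or correct the SD of 0.4. For the percentage primary, state that 120 per arm detects a standardised difference of about 0.36 with 80% power at two-sided 0.05. Translate this into percentage points with an SD that the sponsor can justify.
3. **Data analysis and data management.** Specify one linear mixed model per primary outcome, adjusted for the initial-assessment value and the stratification factors (gender and degree of sick leave). The initial assessment is the baseline that both arms share, because the wait-list group's start-of-treatment value falls at the end of waiting. Replace the ANOVA wording for symptoms with this model, so that it is clear that all randomised patients enter.

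Recruitment closed in May 2021, so the sample size cannot be revisited. The cost is wording only, with no new data. The sponsor gives up the freedom to choose the source of the sick-leave outcome later and reports a lower power for full RTW.

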### Health economic analyses

The primary cost-effectiveness analysis will estimate total costs and QALYs for the 12-month follow-up period of the trial, using an intention-to-treat approach. Service use is not being collected in the trial and the cost-effective analysis will therefore be integrated within the trial and will include intervention costs alone. These will be estimated per patient and will include the cost of staff time, overhead costs and any other materials needed to deliver MCT. QALYs from baseline to follow-up will be estimated using the EQ-5D-5L. A Norwegian value set does not currently exist, and the English value set will be used [65]. EQ-5D-5L responses and index values will be reported and compared to the Norwegian general population norms [66].

Regression analysis will be used to estimate net costs and net QALYs and these estimates will be bootstrapped to generate 10,000 net pairs of costs and QALYs to inform the probability of cost-effectiveness. The incremental cost-effectiveness ratio (ICER), a joint measure of cost and health benefit, will be the key outcome, and a cost-effectiveness plane and cost-effectiveness acceptability curve will be plotted.

As the trial is not collecting service use to inform wider healthcare costs and the time horizon is limited, the economic evaluation will be furthered with the development of a decision analytic economic model which will synthesise trial data with the published literature. The model structure will be drafted considering the existing literature and the trial design, following which it will be reviewed and validated with clinicians. A literature review will be used to identify data not available within the trial (e.g. broader healthcare resource use and costs). As with the trial-based analysis, the key outcome will be the ICER (per QALY).

Guidance of the methods for economic models will be followed and the economic evaluation will adhere to reporting guidelines. Sensitivity analysis will explore uncertainty, in particular, the impact of using alternative measures of benefit, perspectives of cost and time horizons.

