MCT plus work-focused interventions will be superior to the wait-list condition in reducing symptoms of anxiety and depression and the percentage of sick leave. Results will examine post-treatment and for the intervention group at 6 and 12 months follow-upMCT plus work-focused interventions will be cost-effective when compared with the wait-list condition. Self-report data on the percentage of sick leave will examine post-treatment, 6 and 12 months follow-up, in addition with the national register data span from 24 months prior to treatment and 48 months after ending the treatment

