### Secondary objectives

The secondary objective of the study is to determine whether the treatment is cost-effective compared to the wait-list condition and to examine other exploratory outcome measures. The questionnaires will be collected at screening, first treatment session and last treatment session. Follow-up questionnaires will be collected at 6 and 12 months post-treatment. The exception is change in diagnoses which will be evaluated by clinical interview at screening, before the first treatment session and after the last treatment session.

Measurements for the study’s secondary objective:
Changes in quality of life as measured by the EQ-5D-5L [37]Changes in metacognitions as measured by the Metacognitions Questionnaire 30 (MCQ-30) [38]Changes in bullying and victimisation as measured by the Negative Acts Questionnaire [39].Changes in work-related self-efficacy as measured by the Return to Work Self-Efficacy questionnaire (RTW-SE) [40].Changes in resilience as measured by The Resilience Scale for Adults (RSA) [41]Changes in subjective health complaints as measured by the Subjective Health Complaints questionnaire (SHC) [42].Change in diagnoses as measured by the Mini-International Neuropsychiatric Interview (M.I.N.I.) [43].

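### The 12-month cost-effectiveness analysis contrasts immediate with 8- to 12-week-delayed treatment, which is not the stated hypothesis of cost-effectiveness against the wait-list condition

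*Protocol article*

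**What the plan says.** All references are to the Protocol article.

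- **The question.** The second hypothesis, at the end of Background, is that the intervention "will be cost-effective when compared with the wait-list condition". Secondary objectives repeats it: the aim is to "determine whether the treatment is cost-effective compared to the wait-list condition".
- **The analysis.** Health economic analyses states: "The primary cost-effectiveness analysis will estimate total costs and QALYs for the 12-month follow-up period of the trial", by intention to treat. On costs, "the cost-effective analysis will therefore be integrated within the trial and will include intervention costs alone". On the contrast, "Regression analysis will be used to estimate net costs and net QALYs"; these estimates are bootstrapped to 10,000 pairs and the ICER is the key outcome. On benefit, "QALYs from baseline to follow-up will be estimated using the EQ-5D-5L".
- **What controls receive.** The Abstract says: "All patients will receive up to 12 weekly sessions". Randomisation and blinding has half of the wait-list arm start treatment after 8 weeks and half after 12.
- **How follow-up is dated.** Secondary objectives and Retention and follow-up both date the 6- and 12-month questionnaires from the end of treatment.
- **How the clinical comparison is handled.** Sample size estimate compares the treated arm at end of treatment with controls at end of waiting. The first hypothesis confines the 6- and 12-month results to the intervention group.

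**The concern.** The clinical part of the plan stops the between-arm comparison when the wait ends. The economic part runs it over 12 months, during which the control arm receives the therapy under evaluation. The section does not mention this switch and does not rename the contrast.

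Counting intervention costs alone sharpens the problem. Once controls have had their sessions, the only cost item in the analysis is about equal in both arms, whatever the therapy costs. An ICER near zero, with its bootstrap cloud and acceptability curve, could then be reported as showing that treatment costs almost nothing per QALY against a wait-list. The figures would in fact show only that starting 8 to 12 weeks earlier costs little extra.

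This is not a detail left to an analysis plan. The horizon, the cost scope, the key outcome and the hypothesis are all stated, and they do not fit together.

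**Working it through.** The article gives no cost, utility or ICER figure, so there is nothing to reproduce. The check uses its timings and labelled assumptions.

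**Inputs from the article:** waits of 8 and 12 weeks in equal halves (mean 10); up to 12 weekly sessions in both arms; intervention costs only; intention to treat.

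**Assumptions:** a utility gain U builds linearly over 12 weeks of treatment and is then kept; there is no change while waiting; therapy costs C per treated patient; U ranges from 0.05 to 0.20.

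**1. Twelve months counted from randomisation.** A linear 12-week rise loses 6 weeks' worth of full gain. The QALY gain over 52 weeks for a patient who starts after d weeks is therefore U × (52 − d − 6)/52.

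- Immediate start: 46/52 = 0.885U. This is also the gain over an untreated comparator.
- 8-week wait: 38/52 = 0.731U. Difference from immediate: 8/52 = 0.154U.
- 12-week wait: 34/52 = 0.654U. Difference from immediate: 12/52 = 0.231U.
- Average wait-list patient: 36/52 = 0.692U. Difference from immediate: 10/52 = 0.192U.

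As a share of the untreated contrast: 8/46 = 17%, 12/46 = 26%, mean 10/46 = 22%. U cancels.

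| U | Immediate vs delayed (mean wait) | Immediate vs untreated |
|---|---|---|
| 0.05 | 0.010 | 0.044 |
| 0.10 | 0.019 | 0.088 |
| 0.20 | 0.038 | 0.177 |

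**2. Net cost on the same horizon.** If a fraction f of controls start treatment, net cost is (1 − f)C and net QALYs are U × (0.885 − 0.692f).

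- f = 1: net cost 0, ICER 0.
- f = 0.9: 0.1C / 0.262U = 0.38 C/U.
- f = 0.8: 0.2C / 0.331U = 0.60 C/U.
- Untreated comparator: C / 0.885U = 1.13 C/U.

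The values of f below 1 are assumed.

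**3. Twelve months counted from end of treatment.** Each arm's clock starts after its own sessions. Both arms are treated throughout the window and the waiting period lies outside it, so no wait-list contrast remains.

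**4. Comparison stopped at end of waiting.** With a start at week 0, the gain accrued by week w (up to 12) is U × w²/(2 × 12 × 52).

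- Week 8: 64/1248 = 0.051U. With cost pro rata to sessions (8/12 of C), this is 13.0 C/U.
- Week 12: 144/1248 = 0.115U. With cost C, this is 8.7 C/U.

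Against 1.13 C/U over a year, that is about 8 to 12 times higher, because most of the cost is set against little of the benefit.

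**5. Can a common 52-week horizon be built?** With 12 weeks of treatment, the treated arm has EQ-5D-5L near weeks 0, 12, 38 and 64. Controls have it at screening, at week 8 or 12, at week 20 or 24, at week 46 or 50, and at week 72 or 76. Week 52 is bracketed in both arms, so interpolation suffices. This takes the follow-up questionnaires to apply to both arms, as Secondary objectives implies by naming no exception.

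**The case against.** The strongest reply is that wait-list never meant untreated. Study design rejects a no-treatment control on ethical grounds and sets the maximum wait equal to the clinic's average. On that view, immediate treatment versus the usual wait is the policy question, a 12-month intention-to-treat comparison estimates it without bias, and a near-zero net cost is simply the right answer. Much of this stands: the planned comparison is valid for that contrast. What does not follow is that the contrast has been named. Control condition and concomitant care describes the wait-list as receiving no intervention, and Health economic analyses never says that its comparator is treated for most of the year.

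A second reply is that the decision model and the sensitivity analyses on time horizon deal with the matter. They could. But the model is justified by missing service-use data and the limited horizon, no untreated comparator is named for it, and neither element is said to address controls being treated.

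Three stronger readings are tempting but not supported:

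- A reader might infer that the ICER will be overstated 4- to 6-fold (0.885/0.231 = 3.8; 0.885/0.154 = 5.8). That requires leaving out the control arm's therapy costs. The article specifies total costs, estimated per patient, by intention to treat, which would include them.
- A reader might infer that the QALY difference could change sign because the control window runs 8 to 12 weeks longer (0.09-0.14 QALY at an assumed utility of 0.6). The article speaks of a 12-month period and does not state unequal windows.
- A reader might infer that the main analysis should stop at the end of waiting. Step 4 of the working shows that this brings a distortion of its own.

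**Conclusion.** The point holds as a mismatch between the stated hypothesis and the primary economic analysis. Dated from randomisation, the trial-based ICER describes immediate versus 8- to 12-week-delayed treatment. Its QALY difference is 17-26% of that against an untreated comparator, and its net cost is near zero. Dated from end of treatment, it holds no wait-list contrast.

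The percentages rest on the linear 12-week rise and the maintained gain, not on U. Net cost is near zero largely, not wholly, by design, because session numbers vary and patients may stop. That the contrast changes at all rests only on the article's own schedule.

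The analysis is not invalid, and no sign error or multiple-fold ICER error is shown. Cost-effectiveness is a secondary objective, so the clinical primary outcomes and the sample size are untouched. What changes is what the key economic result may be said to show.

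**What to change.** 1. Fix one 52-week horizon from randomisation for both arms. Count the therapy costs of both arms within it, and interpolate EQ-5D-5L from the assessments already scheduled.
2. Restate the estimand, and any conclusion drawn from the trial-based ICER, as immediate versus 8- to 12-week-delayed treatment.
3. Draw conclusions about treatment versus no treatment only from the decision model already planned, with an explicit untreated comparator informed by the waiting phase. State the extrapolation beyond 12 weeks as an assumption.
4. Optionally add an analysis limited to the waiting phase as a sensitivity analysis, not as a replacement for the primary analysis.

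The cost is a rewording of the health-economic section and of the second hypothesis. No new data are needed. The downside is that the trial-based ICER answers a narrower question, and the comparison with no treatment rests on a model.

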## Methods

### Primary objectives

The primary objective of the study is to examine the impact of MCT plus work-focus interventions on symptoms of depression and anxiety and percentage of sick leave at end of treatment. Other measurement points will be included in secondary objectives. Self-report data will be collected at initial assessment, start and end of treatment as well as at 6 and 12 months follow-up. Data from the national registry related to percentage of sick leave is collected up to 24 months prior to and 48 months after treatment. A schematic overview of measurements and endpoints are included in Fig. 2. The following measures will be used:
Changes in the degree of sick leave recorded from National registries (time frame: from 2 years prior to intervention to 4 years after intervention).Changes in the degree of sick leave from patient self-report (time frame: from pre-treatment, to post-treatment (12 weeks), and at 6 months and at 1 year follow-up).Changes in anxiety symptoms as recorded by Beck Anxiety Inventory (BAI) [35] (time frame: from pre-treatment to post-treatment (12 weeks) and at 6 months and 1 year follow-up).Changes in depressive symptoms measured by Beck Depression Inventory II (BDI-II) [36] (time frame: from pre-treatment to post-treatment (12 weeks) and at 6 months and 1 year follow-up).

BDI-II and BAI are self-reported measures. For the percentage of sick leave, both national registry data will be collected from the National Labour and Welfare administration in addition to self-report.

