### Control condition and concomitant care

The control condition in the trial is a wait-list where patients receive no intervention. During the waitlist condition and the intervention, medication is administered by the participant GP in accordance with national guidelines. Use of medication and health services are recorded at assessment, start of treatment and end of treatment through self-report forms. No other psychotherapy will be allowed during the 12-week treatment period of the trial. However, the frequency of accessing additional therapy during the follow-up period will be assessed. Somatic health status, including any somatic diagnoses, is recorded by self-report and will be reported as part of patient characteristics in all publications.

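### The trial-based economic analysis counts intervention costs only because service use is said not to be collected, yet the protocol records service use and registry sick leave and still calls the result total costs

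*Protocol article*

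**What the plan says.** All references are to the protocol article.

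- **Health economic analyses, outcome and horizon:** "The primary cost-effectiveness analysis will estimate total costs and QALYs for the 12-month follow-up period of the trial".
- **Health economic analyses, cost scope:** "Service use is not being collected in the trial and the cost-effective analysis will therefore be integrated within the trial", so that the analysis "will include intervention costs alone". The items named are staff time, overheads and materials for delivering the therapy.
- **Health economic analyses, reason for the decision model:** "As the trial is not collecting service use to inform wider healthcare costs and the time horizon is limited". Wider healthcare use is then to come from a literature review, as an example of data the trial does not have. Sensitivity analyses are to vary the cost perspective and time horizon, among other things.
- **Control condition and concomitant care:** "Use of medication and health services are recorded at assessment, start of treatment and end of treatment through self-report forms". For the later period: "However, the frequency of accessing additional therapy during the follow-up period will be assessed".
- **Primary objectives** (and again under Sick leave in the outcome measures): "Data from the national registry related to percentage of sick leave is collected up to 24 months prior to and 48 months after treatment".
- **Background, hypotheses:** directly after the cost-effectiveness hypothesis comes the sentence beginning "Self-report data on the percentage of sick leave will examine post-treatment, 6 and 12 months follow-up", which goes on to the registry data.
- **Abstract:** total cost and quality-adjusted life-years (QALYs) are named as the outcomes of the cost-effectiveness analysis.

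**The concern.** The cost scope is presented as forced by missing data, not as a chosen perspective. If the data are in fact recorded, that justification falls. An analyst following the economic section as written would leave out service use that the trial records and sick leave that it obtains from registries.

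This matters because the treatment is work-focused. Its economic case rests largely on whether it shortens sick leave and reduces other care, and an ICER whose cost side contains only therapy delivery cannot register either. A reader who sees the result reported as total costs would not know this. The Discussion offers the economic results as input to policy and refers to the societal expense of reduced employment, so the omitted items are the ones that such a reader would look for.

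**Working it through.** No plan figure needs to be reproduced. The check compares the sections and asks what each data source could supply.

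**1. Does the stated reason hold?** One section says service use is not collected. Another says that use of medication and health services is recorded at three time points. As worded, both cannot be true. The second mention in the economic section is softer, since it speaks of service use that would inform wider healthcare costs. It could mean that the forms are too coarse to cost, but the section does not say so.

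**2. Do the recorded points fit the randomised comparison?** Under Study design, the intervention arm starts less than 1 week after assessment and controls wait 8 or 12 weeks. In the intervention arm the start and end forms bracket therapy. In controls the assessment and start forms bracket the wait. Service use is therefore recorded in both arms around the phase in which they differ, although no recall window or units are given.

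**3. How much of a 12-month horizon do the forms span?** Assume 12 weekly sessions and a 52-week year.

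| Arm | Assessment to end of treatment | Share of 52 weeks |
|---|---|---|
| Intervention | up to 1 + 12 = 13 weeks | 13/52 = 25% |
| 8-week wait | 8 + 12 = 20 weeks | 20/52 = 38% |
| 12-week wait | 12 + 12 = 24 weeks | 24/52 = 46% |

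These shares apply if the 12 months run from assessment. If they run from end of treatment, the forms cover none of the period, and only the frequency of additional therapy is left. On either reading the forms cannot supply 12 months of service costs. Registry sick leave, at 48 months after treatment, spans the horizon on both readings.

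**4. What enters the ICER?** Write

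ICER = ΔC / ΔQALY, with ΔC = ΔC(intervention) + ΔC(services) + ΔC(lost production).

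The first term alone is a narrow intervention-cost perspective, the first two a healthcare perspective, and all three a societal one. The trial-based analysis keeps only the first term. The documents give no unit costs, quantities of service use or valuation of sick leave, so neither omitted term can be computed, and its sign cannot be fixed.

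**5. What can be said about the retained term?** During the wait, treated patients incur therapy costs and controls incur none, so ΔC(intervention) is at least zero in that phase. The Abstract says all patients receive up to 12 sessions, and Study design says the number may vary. If the controls' later treatment is counted within the 12 months, the difference could be close to zero or of either sign.

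**The case against.** The strongest defence has four parts.

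- **The forms may not be fit for costing.** They are mentioned under concomitant care, with no recall period, contact types or units, and they stop at end of treatment. This stands as a limit on what can be costed. It does not rescue the statement that service use is not collected.
- **A narrow perspective is legitimate, and sick leave is not service use.** This is correct. A reader might infer that the registry data contradict the economic section directly, and they do not. They bear on the scope in another way: missing service-use data cannot explain leaving out sick-leave costs. The link in the hypotheses is also weak evidence, because the sick-leave sentence follows the cost-effectiveness hypothesis but gives only measurement times and no costing.
- **Wider costs are already provided for.** The decision model combines trial data with literature, and sensitivity analyses will vary the cost perspective. This stands in part, but neither is tied to the service-use forms or the registry, and wider healthcare use is itself the example given of data the trial lacks.
- **Costing detail belongs in the data-analysis plan, which is not shown.** This is true of unit costs and methods. The point here is a reason that the article states and contradicts, and a label that it applies.

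A reader might also take the Background's figure, that 40% of the European cost of mental disorders is due to reduced employment and lost productivity, as the share missing from this ICER. It is an aggregate for all mental disorders across Europe and does not measure incremental cost in this trial.

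**Conclusion.** The concern holds as a contradiction about the data and a mismatch between label and content. The stated ground for counting intervention costs alone conflicts with the protocol's own account of data collection. The result is called total costs although it contains only therapy delivery. The ICER is therefore incomplete for the cost-effectiveness hypothesis.

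The size and direction of the effect cannot be calculated from the documents. Two stronger conclusions are tempting and are not supported. One is that the ICER is wrong: a correctly labelled intervention-cost ratio would be a valid narrow result. The other is that the cost difference is forced to be non-negative: that holds for the waiting phase only, because controls are treated afterwards.

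The conclusion assumes that the forms are used as described. Whether they can be costed is not known. The point concerns a secondary objective and leaves the co-primary outcomes untouched, but it should be settled before the economic analysis is run.

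**What to change.** 1. Reconcile the two sections: state which medication and health-service items are recorded, for which period and recall window, and whether they can be costed.
2. Where the forms allow it, cost the recorded use from assessment to end of treatment (in controls, to end of wait for the randomised comparison). Label it as self-report subject to recall error. If it cannot be costed, say why.
3. Add registry sick leave valued as lost production, as a pre-stated societal-perspective analysis under the sensitivity analysis of cost perspectives already planned.
4. Use literature values only for items and periods that the trial does not record.
5. Call the intervention-only result intervention costs, in the Abstract and the economic section alike.

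The cost is mainly unit-cost work and a stated method for valuing lost production, on data that the protocol already plans to collect. No new data collection is needed. Recall error in the service-use items remains, and the forms will not extend to the full 12 months.
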